#### Data management

Personal information allowing patient identification is neither collected by the app nor transferred in the extract of the DIVI-Protocol. Questionnaires are filled in anonymously by the paramedic staff, and the analysis of the app use is anonymous. All collected data are only accessible for the research team. The research team is aware of data privacy regulations and committed to data protection. Data and information is not shared with other authorities or third parties. All collected data will be permanently destroyed or deleted 10 years after the study.

#### Sample size estimation

The sample size can only be estimated with a high degree of uncertainty because no data are available on language barriers on rescue operations. This underlines the ground-breaking character of the study. Moreover, no calculations are currently available on how paramedics perceive mutual understanding with foreign-language patients. This almost precludes estimating possible treatment effects. Because of the minimal risks to patient safety when the app is used in comparison to randomised controlled trials on drugs and biologics, we aim to include a sufficient number of patients to perform all necessary basal statistical analyses. “Sufficient” here means that even small effect sizes can be detected. Here, 50 to 75 patients in each interventional and control group 1 is described as appropriate [26]. In order to differentiate between the four recruitment sites, a total number of 200 to 300 included patients seems appropriate.

Braunschweig recorded 108 rescue operations per 1000 inhabitants per year and slightly more in an initial reception facility for refugees [15]. The districts of Helmstedt and Wolfenbüttel, where we assume that most of the emergency missions are carried out, are home to 6000 to 7000 foreigners [27]. If 20% of them have only limited German language proficiency [10], 1200 persons could be potential interventional persons. Considering Günther et al. 2016, 130 cases with non-German speaking patients are likely to occur within 1 year. When the crossing motorway corridors and non-German-speaking patients in the surrounding municipalities outside the district are taken into account, it appears possible to recruit an overall number of 400 to 600 patients with language barriers in 1 year.

We expect to receive all DIVI-Protocols of all rescue missions, including those with German-speaking patients for control group 2. This group includes in total 1600 patients at Wendhausen [28], 3500 for Königslutter [29], 6200 for Helmstedt [30], and 3500 for Braunschweig [31], based on the frequencies of served emergency cases in 2018.

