### Clinical trial

In order to evaluate the effect of the developed app, we will conduct a prospective open intervention study. The main purpose of the clinical trial is to assess how the use of the app affects the perceived quality of understanding of non-German-speaking patients from the paramedics’ point of view **(primary outcome)** and how it affects the quality and quantity of information obtained from patients with language barriers **(secondary outcome).** In addition, we will assess whether the tool is perceived as helpful and easy to handle in daily use by the paramedics.

For this purpose, two different patient control groups are recruited and compared with one interventional patient group. Control group 1 consists of German-speaking patients, whereas control group 2 consists of non-German-speaking patients with whom the communication tool is not used. The interventional group consists of non-German-speaking patients with whom paramedics use the tool to communicate with patients. German-speaking control group 1 serves as baseline for on-scene times, intubation rates, and requests for on-scene emergency doctor support. The recruitment period for this group will be at least 12 months because a very large total number of cases is necessary for the selection of matched control groups. By comparing data on control group 2 and on the interventional group, the immediate effect of the tool on communication and information gathering with non-German-speaking patients can be analysed.

As to the primary outcome, we expect that using the tool, paramedics perceive the communication with non-German-speaking patients as easier and more fruitful. Therefore, we will analyse paramedics’ feedback on questionnaires for each emergency drive with foreign-language patients concerning the communication and mutual understanding with patients (see below). Paramedics are asked to report their experience with the tool to assess its acceptance and usability (see above).

Moreover, this study attempts to generate first knowledge about the extent and relevance of language barriers in emergency operations. With regard to the secondary outcome (quality and quantity of information obtained from the patient), we will be able to compare non-German-speaking patients with German-speaking patients and take demographic and medical aspects into account.

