#### Data analysis of the clinical trial

Characteristics of intervention and the two control groups are analysed using descriptive statistics regarding their demografics, medical conditions, assessed communication and native languages (where applicable), and aspects of the emergency operation. Differences between patients of the intervention group and the control groups will be tested for statistical significance using Chi-squared or Mann-Whitney *U*-Tests where applicable. In addition, the groups will be compared according to the recruitment centres in which patients were recruited. Relations between medical aspects of the emergency operation or demographic aspects and the assessed mutual understanding will be analysed using correlation analyses. Changes between control group 2 and the intervention group as to the perceived quality of understanding and to the quantity and quality of obtained information of patients will be analysed using paramedics’ feedback on questionnaires and comparing the content of the free text fields in the DIVI-protocols. In order to enable a comparison between non-German-speaking and German-speaking patients, a control group matched by age, sex, medical condition, and emergency situation will be drawn from the very large group of the German-speaking patients. Then, for example, on-scene times, rates of intubations, and requests for on-scene emergency doctor support can be compared.

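### The sample-size section says that even small effects can be detected and offers 50 to 75 patients per group, a number that does not have this property

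*Protocol article*

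**What the plan says.** All of this is in the protocol article.

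- **Uncertainty (Sample size estimation).** No earlier data exist on language barriers in rescue operations or on how paramedics rate mutual understanding. The section concludes: "This almost precludes estimating possible treatment effects".
- **Criterion (same section).** It nevertheless defines what a sufficient number is: the word "here means that even small effect sizes can be detected".
- **Number (same section).** The next sentence says that "50 to 75 patients in each interventional and control group 1 is described as appropriate", with a literature reference. To differentiate between the four sites, "a total number of 200 to 300 included patients seems appropriate". Later, "it appears possible to recruit an overall number of 400 to 600 patients with language barriers in 1 year".
- **Comparison (Clinical trial).** The effect of the tool is assessed against non-German-speaking controls: "By comparing data on control group 2 and on the interventional group, the immediate effect of the tool on communication" and information gathering can be analysed.
- **Test (Data analysis of the clinical trial).** "Differences between patients of the intervention group and the control groups will be tested for statistical significance using Chi-squared or Mann-Whitney" U-tests.

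**The concern.** The criterion and the number stand in consecutive sentences, so the 50 to 75 per group is presented as meeting the small-effect criterion. This is a positive claim about what the sample can do. It is not a detail left for an analysis plan, and no conventional choice of alpha or power made later would make it true.

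It is also the only statement of sensitivity in the article. A reader who relies on it could take a non-significant primary result as evidence against even a small benefit, when the declared sample would usually miss one.

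**Working it through.** **Inputs from the article.** 50 to 75 per group; 200 to 300 in total; 400 to 600 hoped for in a year; chi-squared or Mann-Whitney tests; intervention group against control group 2.

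**Inputs I assume, because the article does not give them.** Two-sided alpha of 5%, 80% power, 1:1 groups, independent observations, and small taken as d = 0.2 (or w = 0.1 for a 2×2 chi-squared test). Alternatives are checked below.

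**1. The article's own figures.** The total reproduces as sites times the per-group figure: 4 × 50 = 200 and 4 × 75 = 300. The 50 to 75 cannot be reproduced as a number for small effects, as steps 2 to 5 show.

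**2. Number needed for d = 0.2.** n per group = 2(1.960 + 0.842)² / d² = 2 × 7.849 / 0.04 ≈ 393. The t-test version gives 394. For Mann-Whitney, dividing by the relative efficiency 3/π = 0.955 gives 393.4 / 0.955 ≈ 412. This is 394/75 ≈ 5 to 394/50 ≈ 8 times the stated number.

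**3. Difference detectable with the stated number.** d = (1.960 + 0.842) × √(2/n). For n = 50 this is 2.802 × 0.200 = 0.56; for n = 75, 2.802 × 0.163 = 0.46. The t-test gives 0.57 and 0.46.

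**4. Power for d = 0.2.** Power ≈ Φ(d√(n/2) − 1.960). For n = 50: Φ(1.000 − 1.960) = 16.9%. For n = 75: Φ(1.225 − 1.960) = 23.1%. The t-test gives 16.8% and 22.9%, Mann-Whitney about 16.3% and 22.3%, and chi-squared with w = 0.1 gives 17.0% and 23.2%.

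**5. Every sample-size reading in the section** (equal split, two-sided 5%; power from the t-test):

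| Per group | Source | Detectable d, t-test | Detectable d, Mann-Whitney | Power, d = 0.2 | Power, d = 0.5 |
|---|---|---|---|---|---|
| 50 | stated per group | 0.57 | 0.57 | 17% | 70% |
| 75 | stated per group | 0.46 | 0.47 | 23% | 86% |
| 100 | 200 in total | 0.40 | 0.41 | 29% | 94% |
| 150 | 300 in total | 0.32 | 0.33 | 41% | 99% |
| 200 | 400 in total | 0.28 | 0.29 | 51% | >99% |
| 300 | 600 in total | 0.23 | 0.23 | 69% | >99% |

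**6. More generous assumptions.**
- One-sided 5%, d = 0.2: 26% and 34% at 50 and 75 per group; 64% and 79% at 200 and 300 per group.
- Small relaxed to d = 0.3: 32% and 45% at 50 and 75 per group, with 176 per group needed for 80%. Only at 200 to 300 per group does power pass 80% (85% to 96%).
- 50 or 75 intervention patients against all German-speaking cases, 1600 + 3500 + 6200 + 3500 = 14,800: 29% and 41% for d = 0.2.

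The sentence with the per-group number names control group 1, while the effect of the tool is judged against control group 2. That is a separate labelling question and does not alter these results.

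**The case against.** **The planned study is larger than 50 to 75 per group.** This is the strongest point and part of it stands. The section moves on to 200 to 300 in total and to a hoped-for 400 to 600, and it does not say how either divides between the groups. Quoting only 17% to 23% would understate the study. But at an equal split neither total reaches 80% power for d = 0.2. One could go further and suppose 400 to 600 in each of two year-long phases. The section calls the figure an overall number and does not say that, and it offers it only as possible: its own arithmetic supports about 130 cases a year (1200 × 108/1000), and the rest is judgement. Even then the property would belong to that larger sample, not to 50 to 75.

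**The plan admits high uncertainty.** It does, but about the true effect. The standardised difference that a given n can detect needs no prior data.

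**The number comes from a cited source.** That source is not at hand, so nothing can be said about what it meant by appropriate. The point concerns the article's own pairing of criterion and number.

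**The inputs are mine.** True, and they must be labelled as such. The result at 50 to 75 per group holds across the alternatives tried.

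**Stronger readings a reader might infer, which the article does not support:**
- That a benefit of half a standard deviation would easily be missed. Power for d = 0.5 is 70% to 86% at 50 to 75 per group and 94% to 99% at 100 to 150.
- That small effects cannot be detected at all. At the hoped-for recruitment, power for d = 0.2 is 51% to 69%: inadequate by the usual standard, but not nil.
- That the investigators intend to read non-significance as no benefit. Nothing in the article says so; the risk lies with readers of the claim.

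**Conclusion.** The claim is wrong as written and should be corrected. At 50 to 75 per group the study detects a medium effect, d of about 0.57 to 0.46, and has 17% to 23% power for d = 0.2. At 100 to 150 per group the detectable d is 0.40 to 0.32, and at 200 to 300 per group it is 0.28 to 0.23.

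These figures rest on the assumed two-sided 5% level, 80% power, equal groups and d = 0.2. The main conclusion is not sensitive to them: no variant tried makes 50 to 75 per group enough for a small effect. The one combination tried that passes 80% two-sided needs both a looser meaning of small (d = 0.3) and the full hoped-for recruitment.

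The finding does not show that the trial is too small to be worth doing, or that more patients must be recruited. It shows that the stated sensitivity is not what the sample provides.

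**What to change.** In Sample size estimation, remove the statement that even small effect sizes can be detected and put the actual property in its place, for example:

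> Assuming a two-sided 5% test, 80% power and equal groups, 50 to 75 patients per group allow detection of a standardised difference of about 0.57 to 0.46; 100 to 150 per group, about 0.40 to 0.32; and 200 to 300 per group, about 0.28 to 0.23. A difference of 0.2 would need about 394 per group, or about 412 with the Mann-Whitney test. The primary comparison (intervention group against control group 2) will be reported with a 95% confidence interval. A non-significant result will not be taken to exclude a small effect or, at 50 to 75 per group, a moderate one.

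Say in the same place how the 200 to 300 and the 400 to 600 are expected to divide between the intervention group and control group 2, so that the reader knows which figure applies.

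The cost is one paragraph. No extra patients are needed, and no endpoint or test changes. The downside is that the published sensitivity looks less favourable.

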#### Data analysis of the clinical trial

Characteristics of intervention and the two control groups are analysed using descriptive statistics regarding their demografics, medical conditions, assessed communication and native languages (where applicable), and aspects of the emergency operation. Differences between patients of the intervention group and the control groups will be tested for statistical significance using Chi-squared or Mann-Whitney *U*-Tests where applicable. In addition, the groups will be compared according to the recruitment centres in which patients were recruited. Relations between medical aspects of the emergency operation or demographic aspects and the assessed mutual understanding will be analysed using correlation analyses. Changes between control group 2 and the intervention group as to the perceived quality of understanding and to the quantity and quality of obtained information of patients will be analysed using paramedics’ feedback on questionnaires and comparing the content of the free text fields in the DIVI-protocols. In order to enable a comparison between non-German-speaking and German-speaking patients, a control group matched by age, sex, medical condition, and emergency situation will be drawn from the very large group of the German-speaking patients. Then, for example, on-scene times, rates of intubations, and requests for on-scene emergency doctor support can be compared.

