**Methods:**

To consider the complex situations of paramedic care and to meet paramedics’ demands, we use an action-oriented research approach to develop the tool. We include the staff of the participating emergency medical service stations and software designers in our approach. The tool is then used and evaluated within an open interventional, non-randomised study with two control groups. Control group 1 (German-speaking patients) and control group 2 (non-German-speaking patients treated without the tool) are recruited starting from the first study phase. In the second study phase, an intervention group is additionally recruited, i.e. non-German-speaking patients with whom the tool is used.

The primary outcome of the clinical trial is improved communication with non-German-speaking patients in emergencies by means of the communication tool. The secondary outcome is an improved quality and quantity of the collected information. We exploratively observe on-scene times, demands for emergency physicians, and the usage of the intervention. By recording patients’ clinical parameters, we consider the severity of the health restrictions.

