**Fig. 1 Fig1:**
[figure not shown]
Timeline of the study

First, the communication tool will be developed using an action-oriented research approach within the first 12 months of the project. Simultaneously, a clinical study will be prepared and data of two control groups will be recruited. Then, the developed app will be implemented into the emergency service procedures, and the phase of recruiting the intervention group begins. Finally, we will evaluate the obtained data. In the following, the methodological approaches are described in more detail.

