#### Inclusion criteria for patients

Patients who meet the following criteria are eligible to participate in the study:
Control group 1: German-speaking patients of all ages who do not use the app.Control group 2: Non-German-speaking patients of all ages who do not use the app (i.e. within the first period of recruitment and because of drop-out in the second recruitment stage)Interventional group: Non-German-speaking patients of all ages who speak one of the available languages (cp. Table 2) and who are responsive to use the app.

**Table 2 Tab2:** Supported languages

• Arabic: possible dialects are Syrian Arabic, Egyptian Arabic, Moroccan Arabic (spelling Modern Standard Arabic) • Bosnian • Croatian • Czech • Dari • English • French	• Italian • Kurdish: possible dialects are Sorani and Kurmanji • Lithuanian • Pashto • Persian • Polish • Russian • Serbian • Turkish

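### The primary contrast (intervention against control group 2) is non-randomised and selectively filled, yet only unadjusted tests are named for it and matching is reserved for another comparison

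*Protocol article*

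**What the plan says.** **Design.** The Abstract (Methods) describes the study thus: "The tool is then used and evaluated within an open interventional, non-randomised study with two control groups". Both control groups are recruited from the first phase. "In the second study phase, an intervention group is additionally recruited". The text under Fig. 1 gives the same order: "the developed app will be implemented into the emergency service procedures, and the phase of recruiting the intervention group begins".

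**Primary outcome.** The Clinical trial section defines it as the "perceived quality of understanding of non-German-speaking patients from the paramedics’ point of view", and reads the immediate effect of the tool from control group 2 against the intervention group.

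**Who enters which group.** Under Inclusion criteria for patients, control group 2 arises "within the first period of recruitment and because of drop-out in the second recruitment stage". The drop-out criteria keep the app out of emergencies that call for immediate action and out of cases with severely limited consciousness. They assign patients with an unsupported language to control group 2. The recruitment section leaves app use to the paramedic. Eligible patients with whom the app was not used are to be analysed separately.

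**Analysis.** The section Data analysis of the clinical trial states: "Differences between patients of the intervention group and the control groups will be tested for statistical significance using Chi-squared or Mann-Whitney" U-tests, where applicable. The groups are also compared by recruitment centre, and medical and demographic aspects are correlated with perceived understanding. The sentence on the primary contrast, "Changes between control group 2 and the intervention group as to the perceived quality of understanding", names data sources (questionnaires and free-text fields) but no model, matching or restriction. Matching has a different purpose: "In order to enable a comparison between non-German-speaking and German-speaking patients, a control group matched by age, sex, medical condition" and emergency situation.

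**Data.** Table 1 lists year of birth, sex, initial Glasgow Coma Scale (GCS) and initial NACA score. Station is known. Table 1 gives times as hours and minutes and lists no calendar date.

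**The concern.** The authors see that case mix can distort a group comparison, since they match for it. They do so for the German against non-German contrast and name nothing equivalent for the contrast that carries the primary outcome.

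That contrast needs it, because the allocation rules create imbalance. In the second phase the app filter removes the most urgent, least responsive and unsupported-language patients from the intervention group, and on the natural reading many of them go into control group 2. First-phase controls passed through no such filter. If these patients are harder to understand, control group 2 will be rated worse for reasons unrelated to the app, and the bias favours the app.

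The other analyses named do not repair this. A comparison by centre does not deal with severity or language. A correlation between severity and understanding shows that severity matters but does not remove it from the group difference. At stake is whether a significant primary result can be read as an effect of the tool.

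**Working it through.** **The plan's own figures.** The Sample size estimation gives 50 to 75 patients per group and 200 to 300 in total over four sites: 4 × 50 = 200 and 4 × 75 = 300. It states no alpha, power, effect size or SD, so 50 to 75 cannot be reproduced. That section attaches the figure to the interventional group and control group 1. I apply it to control group 2 as an assumption. I also show 150 per group, which is the upper total of 300 split into two equal groups.

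**Check 1: analytic false-positive rate with no true app effect.**

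Assumptions, not in the documents: one covariate correlates 0.4 with the rating, and the groups differ on it by 0.3 to 0.5 SD.

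- Bias = correlation × imbalance: 0.4 × 0.3 = 0.12 SD; 0.4 × 0.5 = 0.20 SD.
- Shift in the test statistic = bias / sqrt(2/n).
- Rejection rate = P(|Z + shift| > 1.96), two-sided 5% (normal approximation for a two-group comparison).

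| n per group | sqrt(2/n) | shift at 0.12 SD | rejects | shift at 0.20 SD | rejects |
|---|---|---|---|---|---|
| 50 | 0.200 | 0.60 | 9% | 1.00 | 17% |
| 75 | 0.163 | 0.73 | 11% | 1.22 | 23% |
| 150 | 0.115 | 1.04 | 18% | 1.73 | 41% |

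**Check 2: simulation of severity imbalance.** A 5-point rating, no app effect, 1,500 runs per setting. Assumed: severe cases are 10% of the intervention group and 30 to 40% of control group 2, and are rated 0.5 to 1.0 SD worse.

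| n per group | Mann-Whitney, unadjusted | linear regression adjusted for severity |
|---|---|---|
| 50 | 8–25% | about 5% |
| 75 | 9–36% | 4–5% |
| 150 | 13–64% | 4–5% |

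**Check 3: simulation of the eligibility filter.** Assumed: a share e of 10 to 30% of non-German-speaking patients cannot use the app, and they are rated 0.5 to 1.0 SD worse.

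- If the two phases are equal in size and second-phase ineligible patients join control group 2, their share there is 2e/(1 + e): 0.2/1.1 = 18% up to 0.6/1.3 = 46%. The bias is 0.18 × 0.5 = 0.09 SD up to 0.46 × 1.0 = 0.46 SD. The unadjusted test rejects in 7–51% (n = 50), 8–69% (n = 75) or 12–94% (n = 150).
- With first-phase controls only, it rejects in 5–26%, 6–34% and 5–61%.
- With control group 2 restricted to eligible patients, it rejects in 4–7% throughout. The simulation error at 5% is sqrt(0.05 × 0.95 / 1500) = 0.6 percentage points.

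Adjustment and restriction each remove the part of the bias they are built for.

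**The case against.** The strongest reply is that the analysis section is being over-read. The named tests follow a description of group characteristics and carry the qualifier that they apply where suitable. The sentence on perceived understanding names no test. The Abstract says severity is taken into account through clinical parameters, and an article may leave covariate lists to an analysis plan that is not shown. This stands in part: the tie between these tests and the primary outcome is an inference. But they are the only tests named for differences between the groups, and the one case-mix control the article fixes is assigned to a different contrast. For the same reason, the absence of an effect estimate with a confidence interval is not a defect in itself.

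Several stronger readings are tempting and are not supported:

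- *All relevant covariates, including date and language, are collected and can be adjusted for at no cost.* Table 1 lists clock times only, and the operational number is deleted once the sources are matched. The questionnaire is in an additional file that is not shown, so a language record for control group 2 cannot be confirmed.
- *Regression on everything would solve the problem.* Unsupported languages never occur in the intervention group, and severely limited consciousness should not occur there either. Without overlap, regression cannot correct the imbalance, so restriction is needed. Month terms would move the contrast onto second-phase controls, the most selected ones, because the first phase has no app users.
- *Adjustment would also save patients.* If covariates explained 20% of the variance, 1/(1 − 0.2) = 1.25 would suggest a 25% gain. That formula presumes covariates unrelated to group, which is not the case here.
- *The groups come from different shares of the four stations.* The stations serve different populations, but no text says that their shares differ between groups.

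The plan also contains partial mitigation: the comparison by centre and the separate analysis of eligible non-users. Neither takes ineligible patients out of control group 2.

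**Conclusion.** The point holds in this form: the contrast behind the primary outcome is non-randomised and largely, though not wholly, sequential. Its control arm is filled partly by patients who did not or could not use the app, and the article names only unadjusted tests for group differences while placing matching elsewhere. Differences in severity and eligibility can therefore pass as an app effect.

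The size is conditional. At the stated 50 to 75 per group the false-positive rate is about 9 to 23%, on an assumed correlation of 0.4 and an imbalance of 0.3 to 0.5 SD. The 18 to 41% range needs 150 per group. The simulations show that a strong eligibility filter could do more harm and a weak one almost none. No document gives the true imbalance, so these figures show sensitivity and do not predict the trial's result. The entry rules suggest a bias in the app's favour, but the documents do not prove it. The change should be made. It does not turn the study into one free of confounding.

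**What to change.** Name the primary analysis in the plan:

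- **Model:** ordinal (proportional-odds) regression of the understanding rating on group, intervention against control group 2, reported as an odds ratio with 95% CI. This assumes an ordinal rating; the questionnaire is not shown.
- **Population:** in both groups, only patients who meet the protocol's own app-eligibility criteria and speak a supported language, as far as the records allow. Check whether the questionnaire records language for control patients.
- **Covariates:** a short list from data already collected, namely NACA and/or GCS, age, sex and station. With three station terms this is about six or seven parameters besides group. A longer list would not suit 50 to 75 per group.
- **Supportive:** the unadjusted Mann-Whitney or Chi-squared test.
- **Not adjusted:** calendar month. Say openly that a time trend and the paramedic's choice to use the app remain uncontrolled.

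The cost is mostly analysis wording. The price in the data is a smaller analysed control group, some loss of precision, and a rule for missing covariates.
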